### Clinical data analysis

All clinical statistical analyses will be performed by independent statisticians who are blinded to group allocation, using SPSS version 26.0 (IBM Corp., Armonk, NY, USA). The primary clinical analysis will focus on the between-group difference in BI change after treatment. Analyses of clinical outcomes will primarily follow the intention-to-treat principle, including all randomized participants according to their allocated group. A per-protocol analysis may also be conducted as a sensitivity analysis in participants who complete the assigned intervention. Missing data will be handled using appropriate statistical methods depending on the extent and pattern of missingness.

Continuous variables will be presented as mean ± standard deviation (SD) when normally distributed or as median with interquartile range (IQR) when non-normally distributed. Categorical variables will be summarized as frequencies and percentages. Between-group comparisons of continuous variables will be performed using the independent-samples t-test for normally distributed data or the Mann–Whitney U test otherwise. Within-group changes over time will be assessed using paired-samples t-tests or Wilcoxon signed-rank tests, as appropriate. For categorical or ordinal variables, the chi-square test, Fisher’s exact test, or rank-sum test will be used as appropriate. Clinically relevant concomitant medications and rehabilitation interventions will be summarized by group using descriptive statistics, with attention to the magnitude and clinical relevance of any between-group differences. If clinically meaningful imbalances in co-interventions are observed, these factors will be considered in the interpretation of the results, and exploratory sensitivity analyses or covariate-adjusted analyses may be performed as appropriate.

For repeated clinical assessments, changes over time and between-group differences will be further evaluated using repeated-measures analysis or an equivalent mixed-effects approach, where appropriate. The relationships between clinical outcome measures and imaging parameters will be assessed using Pearson or Spearman correlation analyses, depending on the distribution of the data. All statistical tests will be two-sided, and a *p*-value < 0.05 will be considered statistically significant.

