**Methods and analysis:**

This is a single-center, randomized, assessor- and statistician-blinded, pragmatic add-on controlled trial. A total of 62 patients with brainstem infarction will be randomly assigned in a 1:1 ratio to a conventional acupuncture group or an adjunctive Shallow Acupuncture group. In keeping with routine inpatient practice in the acupuncture department, both groups will receive standard medical management, routine rehabilitation, and conventional acupuncture, while the adjunctive Shallow Acupuncture group will additionally receive Shallow Acupuncture once daily for 14 consecutive days. The primary clinical outcome will be activities of daily living, assessed by the Barthel Index. Secondary clinical outcomes will include the National Institutes of Health Stroke Scale and the modified Rankin Scale. Exploratory indicators will include measures derived from rs-fMRI and DTI. rs-fMRI analyses will focus primarily on resting-state functional connectivity, whereas DTI analyses will focus primarily on fractional anisotropy; mean diffusivity will be examined as an exploratory diffusion metric. Clinical outcomes will be assessed at baseline, post-treatment, and 1-month follow-up, and neuroimaging assessments will be performed at baseline and post-treatment.

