### Inclusion criteria

Patients meeting all of the following criteria will be included:

Diagnosis of ischemic stroke consistent with the Guidelines for Primary Care of Ischemic Stroke (2021) (28), and brain MRI confirming a single ischemic infarction involving the brainstem, with the lesion confined to one side and not crossing the midline.Men or women aged 50–80 years, with a first-ever stroke and a disease duration ≤ 6 months.NIHSS score ≥ 2, and the presence of at least one assessable brainstem-related neurological deficit, such as dysphagia, dysarthria, vertigo, balance impairment, or ataxia.Clinically stable, without disturbance of consciousness, and able to understand and cooperate with study procedures.Able and willing to provide written informed consent.Not currently participating in any other clinical study.Right-handed prior to stroke onset, as assessed by the Chinese version of the Edinburgh Handedness Inventory (29).

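### The primary Barthel Index comparison does not adjust for baseline and lets the observed distribution choose between a mean and a rank comparison; a single baseline-adjusted mean difference would be a free improvement

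*Protocol article*

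**What the plan says.** Under Clinical data analysis, the protocol article states: "The primary clinical analysis will focus on the between-group difference in BI change after treatment". The rule that then governs a continuous outcome is: "Between-group comparisons of continuous variables will be performed using the independent-samples t-test for normally distributed data or the Mann–Whitney U test otherwise". The summary measure follows the same switch: "Continuous variables will be presented as mean ± standard deviation (SD) when normally distributed or as median with interquartile range (IQR) when non-normally distributed".

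Covariate adjustment of clinical outcomes appears once in that section. It is optional and is tied to imbalance in co-interventions, not to baseline BI: "exploratory sensitivity analyses or covariate-adjusted analyses may be performed as appropriate". A longitudinal analysis is mentioned as an addition: "changes over time and between-group differences will be further evaluated using repeated-measures analysis or an equivalent mixed-effects approach, where appropriate".

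Baseline BI is available for everyone. The abstract says "Clinical outcomes will be assessed at baseline, post-treatment, and 1-month follow-up", and Table 1 schedules BI at all three visits. Primary outcome measures describes BI as running from 0 to 100. Sample size calculation plans a two-sample equal-variance t-test on a mean difference of 4.84 points with a common SD of 5.22.

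**The concern.** Two features of the stated rule are weak.

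**No baseline adjustment.** A change score subtracts baseline, but on a bounded scale the amount gained usually still depends on the starting value. Entry is broad: NIHSS of at least 2 with no upper limit, "with a first-ever stroke and a disease duration" of up to 6 months. Baseline BI may therefore vary widely. Whatever correlation remains between baseline and gain adds avoidable noise, and a chance imbalance in baseline BI carries that part into the estimate. A covariate that is already collected would remove it.

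**A switch of test and summary on the observed distribution.** The t-test compares means. Mann–Whitney compares ranks and would be reported with medians and IQRs. The trial was sized on a mean difference, but under the rule the reader may receive no mean difference to set against 4.84. Because no other primary test is named and the sample size rests on a t-test, this general rule is the one that applies to BI change.

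**Working it through.** **1. Reproduce the plan's sample size.** Inputs from Sample size calculation: δ = 4.84, σ = 5.22, two-sided α = 0.05, power 90%, 1:1 allocation, 15% dropout.
- Printed formula: 2 × (1.960 + 1.282)² × 5.22² / 4.84² = 24.4, so 25 per group.
- Exact noncentral t: power 0.895 at 25 and 0.906 at 26 per group, so 26, as stated.
- Dropout: 26 / 0.85 = 30.6, so 31 per group and 62 in total, as stated.

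The sample size is not in error.

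**2. What baseline adjustment would add.** The correlation ρ between baseline and Day-14 BI is not in the article, so a range is assumed. With equal variances at the two visits, the variance of the ANCOVA estimate relative to the change-score estimate is (1 + ρ)/2. The change SD is held at 5.22. The unadjusted SE at 26 per group is 5.22 × √(2/26) = 1.448. ANCOVA power uses 2n − 3 = 49 degrees of freedom. Since 5.22² = 2 × SD² × (1 − ρ), each ρ also fixes the baseline SD.

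| ρ | Implied baseline SD | Variance ratio | SE | Power at 26 per group |
|---|---|---|---|---|
| unadjusted | – | 1 | 1.448 | 0.906 |
| 0.5 | 5.2 | 0.75 | 1.254 | 0.966 |
| 0.8 | 8.3 | 0.90 | 1.373 | 0.932 |
| 0.9 | 11.7 | 0.95 | 1.411 | 0.920 |
| 0.966 | 20.0 | 0.983 | 1.435 | 0.911 |

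The gain is material if baseline BI is fairly homogeneous and small if it is widely spread, provided 5.22 is the right SD of change.

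**3. Residual effect of a chance imbalance.** Under the same assumptions, change falls by (1 − ρ) points per baseline point. With 31 per group, a 1-SE baseline difference shifts the unadjusted estimate by (1 − ρ) × SD × √(2/31):
- ρ = 0.5: 0.5 × 5.22 × 0.254 = 0.66 points (14% of 4.84).
- ρ = 0.8: 0.2 × 8.25 × 0.254 = 0.42 points (9%).
- ρ = 0.966: 0.034 × 20.0 × 0.254 = 0.17 points (4%).

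**4. How often the switch would operate.** The article names no normality criterion. Two assumptions are needed: Shapiro–Wilk at 0.05 in each arm, and BI scored in 5-point steps. In 4,000 simulated trials per setting, with 26 per group:
- Exactly normal, unrounded gains: about 10% of trials go to Mann–Whitney.
- Gains with SD 5.22 on a 5-point grid: about 95–98% do, depending on whether the 0–100 bounds are also imposed.
- Type I error of the two-stage rule: 0.047–0.053.
- The two tests disagree on significance in about 2–6% of trials.

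The result is sensitive to the SD. With 31 per group and a 5-point grid, at least one arm fails the test in 99% of trials at SD 5.22, 62% at SD 8 and 39% at SD 10.

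**The case against.** The strongest defence is that nothing here is invalid. Under randomisation the unadjusted change-score comparison is unbiased, and its SE already allows for chance imbalance. The target is stated, the decision rule is written in advance, and statisticians blinded to group labels apply it. Type I error stays near 5% and the two tests seldom disagree. Final covariates are often left to an analysis plan, which is not shown. All of this stands, and it limits the point to efficiency and to a fixed effect measure. It does not remove the point, because the article states a rule, and that rule can replace the planned mean difference with a rank comparison.

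Several stronger readings are tempting but unsupported:
- *The plan ignores baseline BI.* It does not; a change score subtracts it. What is missing is adjustment for the remaining association.
- *Large precision gains and large imbalance shifts together.* One might pair a baseline SD of 20 with ρ of 0.5–0.8. With a change SD of 5.22 and equal variances these are incompatible: SD 20 implies ρ of about 0.966, and ρ of 0.5–0.8 implies a baseline SD of 5.2–8.3. A slope of 0.3 on a baseline SD of 20 is impossible, since 0.3 × 20 = 6.0 exceeds 5.22.
- *The longitudinal analysis contradicts intention-to-treat.* The text offers "repeated-measures analysis or an equivalent mixed-effects approach, where appropriate". It does not specify a complete-case ANOVA, it allows a mixed model, and this is not the primary analysis.
- *The switch is certain.* It is likely only under the scoring and normality-test assumptions above.

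**Conclusion.** The point holds as a no-cost improvement. The stated rule compares BI change without baseline adjustment and lets the data choose between a mean difference and a rank comparison, although the trial is sized on a mean difference of 4.84. Validity, type I error and the planned 62 patients are not in doubt.

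The size of the precision gain is unknown from the article. It runs from a 25% reduction in variance at ρ = 0.5 to under 2% near ρ = 0.97, conditional on a change SD of 5.22 and equal variances. The loss of an estimate in BI points is the firmer part: it follows directly from the written rule whenever the data are judged non-normal.

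**What to change.** Name one primary analysis: ANCOVA of Day-14 BI on group and baseline BI, reporting the adjusted mean difference with a 95% CI, using robust or bootstrap standard errors, whatever a normality test shows. Remove the distribution-triggered switch for the primary outcome and keep Mann–Whitney as a sensitivity analysis only. For Day 14 and 1 month together, commit to the mixed-effects option the article already allows, with baseline BI as a covariate.

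The cost is wording in the analysis section, settled before unblinding. No new data, visits or patients are needed, and the sample size can stay as it is.

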### Sample size calculation

The sample size for the clinical component was calculated based on the primary clinical outcome, namely the between-group difference in Barthel Index (BI) improvement after treatment. According to previous literature (30), the mean increase in BI after conventional acupuncture was approximately 12.66 points. Because no prior study has specifically evaluated the effects of Shallow Acupuncture in patients with brainstem infarction, the expected effect size for the present study was informed by a preliminary pilot study conducted in patients with brainstem infarction treated in the Department of Acupuncture of The Second Affiliated Hospital of Guangzhou University of Chinese Medicine. In these patients, who received Shallow Acupuncture combined with conventional acupuncture, the mean increase in BI after 2 weeks of treatment was approximately 17.5 points, with a standard deviation of 5.22. The clinical sample size was estimated in PASS using the Two-Sample T-Tests Assuming Equal Variance procedure. For transparency, the conventional planning formula is shown below:

$$n=\frac{2{\left(Z_{1-\alpha /2}+Z_{1-\beta }\right)}^{2}\sigma^{2}}{\delta^{2}}$$

where n denotes the required sample size per group, *δ* denotes the expected between-group difference in BI improvement, and *σ* denotes the assumed common standard deviation. In the present study, the expected between-group difference was set at 4.84 points (17.50–12.66). Because no published estimate of the standard deviation of BI change was available for the control condition, a common standard deviation of 5.22, derived from preliminary pilot observations, was assumed for planning purposes. Using a two-sided significance level of 0.05, 90% power, and a 1:1 allocation ratio, PASS estimated that 26 participants per group (52 participants in total) would be required. Assuming a dropout rate of 15%, the final planned sample size was set at 62 patients, with 31 participants in each group.

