### Secondary outcome measures

Secondary outcome measures will include the National Institutes of Health Stroke Scale (NIHSS) and the modified Rankin Scale (mRS).

National Institutes of Health Stroke Scale (NIHSS): The NIHSS (37) is a brief, convenient, and reliable scale for assessing neurological deficits in patients with stroke. It will be used to evaluate the severity of neurological impairment and changes in neurological status over the course of the intervention.

Modified Rankin Scale (mRS): The mRS (38) is a 7-point scale (0–6) used to assess the degree of functional disability and global outcome after stroke. It primarily reflects the level of functional independence, including bodily function, mobility, and participation in activities of daily living.

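### The shared test list for categorical and ordinal variables does not keep order-ignoring tests away from the mRS, and a baseline-adjusted ordinal model would be a cheap improvement

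*Protocol article*

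**What the plan says.** The between-group rule that covers the mRS as an ordinal variable is one sentence under Clinical data analysis. It opens with "For categorical or ordinal variables, the chi-square test" and reads in full: "For categorical or ordinal variables, the chi-square test, Fisher’s exact test, or rank-sum test will be used as appropriate". The section names no test for the mRS itself.

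Under Secondary outcome measures the mRS is one of two secondary clinical outcomes and is clearly ordered: "The mRS (38) is a 7-point scale (0–6) used to assess the degree of functional disability and global outcome after stroke". Table 1 schedules it at baseline, Day 14 and the 1-month follow-up, so every patient should have a baseline grade.

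For outcomes measured repeatedly, Clinical data analysis adds that "changes over time and between-group differences will be further evaluated using repeated-measures analysis or an equivalent mixed-effects approach, where appropriate". No model suited to an ordinal outcome is named there.

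**The concern.** For continuous variables the same section gives a rule for choosing between tests: the t-test if the data are normal, Mann–Whitney otherwise. For ordinal variables it gives none. A two-by-k chi-square or Fisher test treats the mRS grades as unordered labels and spreads the comparison over up to k − 1 degrees of freedom. A rank-sum test concentrates on a shift in one direction. An analyst using either would be within the text as written, although the two tests have different power against the consistent shift towards less disability that one would hope to see.

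There is also a missed opportunity. Applied to the post-treatment grade, all three tests ignore baseline mRS, which usually predicts the later grade well. None of them yields an effect size with an interval, which a reader of a small, preliminary trial needs more than a p-value.

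**Working it through.** **Inputs from the Protocol article.** From Sample size calculation: difference in Barthel Index change 4.84, SD 5.22, planned with "Using a two-sided significance level of 0.05, 90% power, and a 1:1 allocation ratio"; 26 evaluable and 31 randomised per group; 15% dropout. The mRS has grades 0–6. Clinical data analysis sets a two-sided 0.05 level.

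**Inputs not in the documents (assumed).** The mRS distribution, the treatment effect on it and the correlation between baseline and later grade.

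**Step 1: the plan's own figure.** n = 2(1.960 + 1.282)² × 5.22² / 4.84² = 24.4, so 25 per group by the normal approximation. The exact two-sample t solution is 25.44, so 26 per group (power 90.6%). Then 26/0.85 = 30.6, rounded up to 31, and 52/0.85 = 61.2, rounded up to 62. The stated sample size reproduces. It concerns the Barthel Index only; no power is stated for the mRS.

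**Step 2: chi-square against rank-sum on the post-treatment grade.** 40,000 simulated trials per setting, proportional-odds shift, Pearson chi-square on the full table against the tie-corrected rank-sum test. Entries are power, chi-square / rank-sum.

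| Occupied grades | n per arm | OR 2 | OR 3 | OR 4 |
|---|---|---|---|---|
| 6 | 26 | 12.6% / 27.7% | 30.5% / 58.5% | 48.6% / 77.8% |
| 6 | 31 | 15.1% / 32.6% | 37.2% / 66.6% | 58.6% / 84.8% |
| 5 | 26 | 15.0% / 28.2% | 34.8% / 58.2% | 53.7% / 77.9% |
| 5 | 31 | 17.7% / 32.3% | 42.0% / 65.7% | 63.6% / 84.7% |
| 4 | 26 | 17.3% / 27.7% | 39.2% / 56.9% | 58.8% / 76.7% |
| 4 | 31 | 20.4% / 31.7% | 46.9% / 65.1% | 68.1% / 83.9% |
| 3 | 26 | 20.2% / 26.0% | 44.4% / 54.9% | 63.3% / 73.4% |
| 3 | 31 | 23.7% / 31.0% | 51.6% / 62.5% | 71.9% / 81.4% |

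The largest relative loss is 1 − 12.6/27.7 = 55% (6 grades, 26 per arm, OR 2). The smallest is 1 − 71.9/81.4 = 12% (3 grades, 31 per arm, OR 4). With no effect (OR 1), chi-square rejects in 4.0–5.1% of trials and rank-sum in 4.9–5.1%.

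**Step 3: cross-checks.** The extension of Fisher's test to more than two grades, at 31 per arm (600 simulated trials), has power 40–47% at OR 3 and 61–76% at OR 4, against 63–67% and 81–85% for rank-sum. By noncentral chi-square theory, an effect with 80% power on 1 degree of freedom has 71%, 65%, 60% and 56% on 2, 3, 4 and 5 degrees of freedom.

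**Step 4: using the baseline grade.** Simulation with a fitted proportional-odds model on arm and baseline mRS. Assumed: 29 per arm (between the 26 evaluable and 31 randomised), latent shift 0.6 SD, correlation of baseline with later score 0.4–0.8, 4 to 6 grades.

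| Analysis | Power |
|---|---|
| Chi-square, post-treatment grade | 28–38% |
| Rank-sum, post-treatment grade | 51–56% |
| Rank-sum, change in grade | 43–85% |
| Proportional odds with baseline mRS | 62–92% |

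Type I error of the model was 5.0–6.4%, so slightly above nominal in places.

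**The case against.** The strongest reply is that the suitable test is already listed. Two variable types share a short list with a qualifier that leaves the choice to fit, and the natural reading is chi-square or Fisher for categorical variables and rank-sum for ordinal ones. That stands. A reader might infer that the plan prescribes an order-ignoring test for the mRS, or gives it priority because it comes first. The text supports neither.

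A reader might also infer that power for the mRS would be roughly halved. That is close to true only with six occupied grades at OR 2–3, or five at OR 2. With four grades chi-square keeps 62–81% of the rank-sum power, and with three 76–88%. The documents give no mRS distribution, so none of these cases can be singled out.

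Further, the test for each secondary outcome is commonly fixed in a statistical analysis plan, which is not shown, and the repeated-measures provision could use baseline and give an estimate. Both points lower the weight. They do not remove the point: the published sentence still pools the two variable types, and the repeated-measures analysis is conditional, supplementary and not tied to an ordinal model.

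Finally, tying the mRS to the rank-sum test would alone remove the ambiguity. That is correct. The ordinal model is recommended for its gain in power and its effect estimate, not because rank-sum would be wrong.

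**Conclusion.** This holds as a low-severity, cheap improvement. The sentence leaves an order-ignoring test open for a named secondary outcome and does not exploit the baseline grade. Choosing chi-square would cost about 12–55% of the rank-sum power, on the assumption of 3–6 occupied grades and an odds ratio of 2–4. Moving from rank-sum on the post-treatment grade to a baseline-adjusted proportional-odds model would raise power from about 51–56% to about 62–92% under the assumptions of Step 4. That second gain comes from baseline adjustment, which is a separate matter from respecting the order of the grades, and it grows with the baseline correlation.

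The trial is sized on the Barthel Index alone. No stated power for the mRS is contradicted, and the primary analysis and the sample size are unaffected.

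**What to change.** Under Clinical data analysis:

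- Limit the chi-square and Fisher's exact tests to nominal variables.
- State that mRS at Day 14 and at 1 month is compared by proportional-odds (ordinal logistic) regression on arm and baseline mRS, reported as a common odds ratio with 95% CI.
- Keep the rank-sum test as the fallback if the model does not fit.

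The cost is a sentence or two of text. Baseline mRS is already scheduled, and ordinal regression is available in the named software. The downside is a proportional-odds assumption that is hard to check with about 26–31 patients per arm, and a type I error that reached 6.4% in simulation.

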### Neuroimaging data analysis

Neuroimaging analyses will be conducted in the predefined imaging subgroup and will be considered secondary and exploratory. Given its potential influence on rs-fMRI and DTI measures, age will be considered as a covariate in exploratory neuroimaging analyses where appropriate. Resting-state fMRI data will be preprocessed using SPM12 (Wellcome Trust Centre for Neuroimaging, London, UK) running on the MATLAB platform. The preprocessing pipeline will include slice-timing correction, head-motion correction, spatial normalization to Montreal Neurological Institute (MNI) space, and spatial smoothing.

rs-fMRI analyses will focus primarily on resting-state functional connectivity (FC). Independent component analysis (ICA) will be performed using the Group ICA of fMRI Toolbox (GIFT). The analysis will include dimensionality reduction, ICA decomposition, and component back-reconstruction. The number of independent components will be estimated according to the minimum description length criterion, and the Infomax algorithm will be used for ICA decomposition. Component stability will be evaluated using ICASSO, and components with a stability index > 0.90 will be retained. Spatial maps will then be converted into z-score maps, and functionally meaningful resting-state networks will be identified by comparison with standard network templates.

DTI data will be processed using the FMRIB Software Library (FSL, Oxford, UK). Preprocessing will include eddy-current correction, head-motion correction, and registration to standard space. DTI analyses will focus primarily on fractional anisotropy (FA), with particular attention to the corticospinal tract (CST) and other major motor-related white matter pathways. Mean diffusivity (MD) will be examined as an exploratory diffusion metric. Group comparisons of diffusion indices will be performed using the Randomise tool in FSL, with permutation-based nonparametric testing and threshold-free cluster enhancement (TFCE) for multiple-comparison correction. For imaging analyses, results will be interpreted primarily as exploratory, and corrected *p*-values < 0.05 will be considered statistically significant.

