To investigate whether adjunctive Shallow Acupuncture is accompanied by treatment-related neural changes after brainstem infarction, rs-fMRI and DTI provide complementary approaches for evaluating brain network reorganization and white-matter microstructural changes. Blood oxygen level–dependent functional magnetic resonance imaging (BOLD-fMRI), which indirectly reflects neuronal activity by detecting blood oxygen–dependent signals, has become a key tool for investigating brain functional activity (20). Previous studies have shown that patients with brainstem infarction exhibit abnormalities in resting-state network connectivity, and that these changes may be associated with functional recovery (21–23). Diffusion tensor imaging (DTI), by quantifying the diffusion properties of water molecules, enables assessment of white matter tract integrity (24). Fractional anisotropy (FA), a commonly used DTI parameter, has been shown to decrease after brainstem infarction, particularly in the corticospinal tract (CST), and subsequent FA recovery may be associated with more favorable motor outcomes (25–27).

Together, rs-fMRI and DTI may help characterize brain network reorganization and white-matter microstructural changes after brainstem infarction, thereby providing a multimodal framework for exploring clinical–imaging associations in response to adjunctive intervention. Against this background, the present randomized controlled trial is designed to evaluate the adjunctive effectiveness of Shallow Acupuncture in patients with brainstem infarction within routine integrative inpatient care. We hypothesize that, compared with standard care plus conventional acupuncture alone, adjunctive Shallow Acupuncture will be associated with greater improvement in activities of daily living and may be accompanied by changes in resting-state functional connectivity and white-matter microstructural integrity as assessed by rs-fMRI and DTI.

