For the neuroimaging component, a formal sample size calculation was not considered feasible because of the heterogeneity of rs-fMRI/DTI analysis methods and the exploratory nature of the imaging analyses. Therefore, the imaging sample size was determined pragmatically with reference to prior neuroimaging literature (31–33), in which 12 participants per group have often been regarded as a minimum for obtaining stable estimates. To enhance reliability and to allow for potential data loss due to motion artifacts or incomplete scans, 20 participants per group will be included in the rs-fMRI/DTI analyses.

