### Outcome measures

At baseline, demographic and clinical characteristics will be collected for all participants, including age, sex, educational level, occupation, and disease duration. In addition, the types and spatial distribution of pathological response points in the temporal and occipital regions will be documented.

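### The clinical–imaging correlations are unadjusted for time since stroke, a plausible common cause that is already recorded; the randomised imaging comparison loses only precision by the omission

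*Protocol article*

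**What the plan says.** Under Neuroimaging data analysis, the protocol article states that "age will be considered as a covariate in exploratory neuroimaging analyses where appropriate", giving as its reason that age may influence the MRI measures. No other covariate is named for the FA, mean diffusivity (MD) or connectivity analyses.

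Under Clinical data analysis: "The relationships between clinical outcome measures and imaging parameters will be assessed using Pearson or Spearman correlation analyses, depending on the distribution of the data". No adjustment is attached to these correlations, and the same section sets two-sided p < 0.05 as significant for all tests. The only covariate adjustment it mentions concerns imbalance in co-interventions.

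Three other places bear on this:

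- **Inclusion criteria:** patients qualify "with a first-ever stroke and a disease duration ≤ 6 months"; no lower limit is given.
- **Introduction:** FA is reported to fall after brainstem infarction, and "subsequent FA recovery may be associated with more favorable motor outcomes". The Introduction and Discussion also link connectivity changes to functional recovery.
- **Outcome measures:** baseline data are collected "including age, sex, educational level, occupation, and disease duration". No described analysis uses disease duration, and the Randomization section describes no stratification by it.

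For size, Sample size calculation says that "20 participants per group will be included in the rs-fMRI/DTI analyses", which gives 40 imaged patients over the two arms.

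**The concern.** The reason given for adjusting for age applies at least as well to time since stroke. By the article's own account, imaging measures move during natural recovery, and that movement goes with clinical recovery. A patient scanned in the first weeks and one scanned in the fifth month are at different points of that process, whatever their arm.

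A correlation between a clinical and an imaging measure is not a randomised contrast. If both measures depend on time since stroke, they will correlate even when neither depends on the other and the treatment does nothing. The Discussion presents the framework for clinical–imaging associations as one of the protocol's two main strengths, so such a result would be prominent and could be read as a neural correlate of the intervention.

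**Working it through.** The plan has no figure of its own to reproduce here: the article says that no formal sample size calculation was made for imaging. The documents also give no correlation between time since stroke and FA, connectivity or the Barthel Index. The variance shares below are therefore assumptions, shown over a range.

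**1. Correlation induced by a common cause**

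Let x be the imaging measure, y the clinical measure and t time since stroke (suitably scaled). Suppose t explains a share R² of the variance of each, and nothing else links them. Then

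ρ = r(x,t) × r(y,t) = √R² × √R² = R².

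The chance that a two-sided 5% test rejects follows approximately from Fisher's transformation: with m = atanh(ρ) × √(n − 3), it is P(Z > 1.96 − m) + P(Z < −1.96 − m).

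Example for R² = 0.20, n = 40: atanh(0.20) = 0.2027; m = 0.2027 × √37 = 1.233; P(Z > 0.727) + P(Z < −3.193) ≈ 0.234.

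Simulation with normal x, y and t agrees:

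| Assumed R² | Induced ρ | n = 40: Fisher | n = 40: simulated | n = 20: Fisher | n = 20: simulated | Partial correlation on t |
|---|---|---|---|---|---|---|
| 9% | 0.09 | 8.5% | about 9% | 6.6% | about 7% | about 5% |
| 20% | 0.20 | 23% | 24% | 13% | 13–14% | about 5% |
| 30% | 0.30 | 47% | 48% | 25% | 25% | about 5% |
| 40% | 0.40 | 73% | 74% | 42% | 43% | about 5% |

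The n = 40 columns apply if the arms are pooled, the n = 20 columns to one arm. The article does not say which is meant.

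**2. Sign**

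The induced ρ is a product of two loadings. If the Barthel Index gain is largest early while FA is still falling, the loadings have opposite signs and ρ is negative; if both improve together, it is positive. With linear loadings of the same size, the two-sided rejection rate is the same either way. For a course that falls and then recovers, a single linear loading is only a rough description, which is why the time term should be allowed to be non-linear.

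**3. Randomised comparison, 20 against 20**

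With no treatment effect, simulated type I error was about 5% both with and without time since stroke as a covariate, at assumed correlations of 0, 0.3, 0.5 and 0.7 between time and outcome. For an assumed effect of 0.8 SD, power was:

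| Correlation of time with outcome | Unadjusted | Adjusted |
|---|---|---|
| 0.3 | about 69% | about 72% |
| 0.5 | about 69% | about 80% |
| 0.7 | about 70% | about 93% |

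**4. Chance imbalance**

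Assume duration is uniform over 0 to 182 days. Its SD is 182/√12 = 52.5 days. The difference in arm means at 20 per arm has SD 52.5 × √(2/20) = 16.6 days, and in 95% of trials its absolute size is below about 1.96 × 16.6 ≈ 32 days. A difference of at least half an SD occurs in about 11% of trials.

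**The case against.** The strongest reply has four parts.

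- **Randomisation.** A reader might infer that time since stroke alone could cancel or create the FA and connectivity findings between the arms. The documents do not support that. Allocation is random, so duration is balanced in expectation, and step 3 shows no inflation of type I error. This part of the reply stands in full, provided that selection into the imaging subgroup is unrelated to allocation.
- **Open wording.** Considering age where appropriate does not exclude other covariates, and a condensed article may leave modelling detail to an analysis plan. That is fair as far as it goes. But the article does fix the correlation method, and it singles out one covariate for a reason that applies equally to another variable it collects. This is a better choice available at almost no cost, not a complaint about missing detail.
- **Exploratory status.** The imaging work is labelled exploratory, and the Discussion frames the modalities as characterising changes that go with recovery. The label rightly limits the claims. It does not remove a shared cause from a test that will be called significant at p < 0.05.
- **Undocumented size and form.** The variance shares are assumed, and at the low end (9%) the excess over 5% is small. The article does not say whether the correlations use change scores, and it says only that FA recovery may go with better motor outcome, not that every patient follows one course. All of this stands. It limits how firmly the size and the sign can be stated, not the direction of the recommendation.

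**Conclusion.** The point holds for the clinical–imaging correlations. Time since stroke is a plausible common cause on the article's own account, entry spans up to 6 months, and the stated tests do not adjust for it. Under the assumption of a shared dependence explaining 9% to 40% of each measure and no other link, the false-positive rate is about 9% to 74% at n = 40 and about 7% to 43% at n = 20, against about 5% after correct adjustment. Whether a spurious correlation would be positive or negative cannot be told from the documents.

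For the randomised FA, MD and connectivity comparisons the consequence is milder: lower power, and chance imbalance in duration that goes uncorrected at 20 per arm. The primary outcome is not touched. The change should be made because it is cheap and prevents misreading of a prominent exploratory result.

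**What to change.** - **Imaging models:** name baseline disease duration beside age as a covariate in the Randomise FA and MD models and in the ICA connectivity comparisons, in log days since onset or another non-linear form.
- **Clinical–imaging relationships:** replace the bivariate Pearson or Spearman coefficients with partial correlations (rank-based where needed) or regressions adjusted for disease duration and, where the arms are pooled, for treatment arm. Where change scores are used, add the baseline value.
- **Reporting:** give unadjusted and adjusted estimates with confidence intervals. Describe an association that weakens on adjustment only as consistent with shared dependence on time since stroke. It should not be called proven natural recovery, since at this sample size weakening may also reflect lost precision.

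No new data are needed, because disease duration is already recorded. The cost is a change of analysis wording and about one degree of freedom per added covariate.
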